**Figure 1 F1:**
[figure not shown]
shows the OPTIMA study flow chart.

Chest and abdominal X-rays will be evaluated by the treating physician. Both US and CT are performed and evaluated by radiological residents or radiologists, blinded for each others test results and for the test results of the abdominal and chest X-rays. Summarized clinical findings, as in routine practice, will be provided to the radiologist. The radiologist performing the ultrasound will record the findings in the patients CRF with general and organ-specific US findings ending with a differential diagnosis with a level of confidence of the most likely diagnosis. Another radiologist evaluates the CT scan and records data in a similar way.

### Outcome measures

#### Follow up

Six months of follow up will be obtained for all patients. All available information will be gathered, including course of disease, laboratory findings, operation reports, pathology reports, treatment outcome and costs.

#### Reference standard

All included patients will be evaluated using a uniform reference standard not dependent of the index tests results. An expert panel will review each case and assign the final diagnosis. Cases will be presented in a standardized way, including all available follow-up data gathered as mentioned above. Panel members will evaluate cases individually, after which consensus is reached in group discussion. These final diagnoses will be classified as urgent, defined as a diagnosis which requires treatment within 24 hours, or as non-urgent. The distribution of conditions based on urgency is presented in table 1.

**Table 1 T1:** Urgency classification of diagnoses

**Urgent**	**Non-urgent**
Acute appendicitis	Cholecystolithiasis
Acute diverticulitis	Obstipation
Perforated vicus	Gastrointestinal disorders^∥^
Bowel obstruction/ileus	Hepatic disorders^¶^
Bowel ischemia	Malignancy**
Inflammatory bowel disease	Gynaecological disorders^††^
Peritonitis	Renal and urinary tract disorders^‡‡^
Acute cholecystitis	Non-specific abdominal pain
Cholangitis	
Pancreatitis (acute and chronic)	
Abscess*	
Renal and urinary tract disorders^†^	
Gynaecological disorders^‡^	
Extra-abdominal disorders^§^	

* Intra-abdominal abscess, retro-peritoneal abscess, hepatic abscess, tubo-ovarian abscess

^† ^Renal and ureteral stones with obstruction, hydronephrosis, pyelonephritis

^‡ ^Adnexal torsion, pelvic inflammatory disease, bleeding/rupture ovarian cyst

^§ ^Pneumonia, myocardial infarction, mediastinitis

^∥ ^Gastritis, gastroenteritis, peptic ulcer, acute epiploic appendagitis

^¶ ^Hepatitis, hepatic metastases

** Pancreatic, intestine and kidney malignancies

^†† ^Ovulation pain/bleeding, endometriosis, menstrual pain, uterine myoma

^‡‡ ^Renal and ureteral stones without obstruction, urinary tract infection

### Data analysis

In the analysis, focus will be on the added value of plain X-ray, US and CT over clinical history, physical examination and laboratory findings, in the timely identification of urgent conditions. For this purpose, the findings from the respective imaging techniques will be cross-classified with the urgency categorization. To make head-to-head comparisons between modalities, sensitivities, specificities, likelihood ratios and predictive values will first be calculated for each imaging technique separately.

Next, we will evaluate the diagnostic performance of more detailed diagnostic algorithms. These diagnostic algorithms will be developed using logistic regression modelling. Additional models will look at the incremental gains in the detection of urgent conditions or at the rightful refutation of suspected urgent conditions through imaging modalities and combinations of imaging modalities. A guiding principle is that, in case of equality in diagnostic performance, the diagnostic strategy associated with fewer costs and lower patient burden is to be preferred.

Efficacy of imaging strategies will be investigated for specific patient profiles based on for example age, gender, localisation of pain and organ failure found at physical and/or laboratory examination. A diagnostic strategy may therefore alter for different patient profiles.

Subgroup analysis for specific, frequently occurring, diagnosis will be performed. For example, sub-group analysis for patients diagnosed with appendicitis or diverticulitis. Such analyses will use logistic regression modelling to identify predictive diagnostic variables in the clinical history, physical examination and laboratory findings. As we expect to include a substantial number of patients with non-specific abdominal pain, another analysis will be focussed on the early identification of this subgroup. Herewith also logistic regression modelling will be used to identify discriminate factors in history, physical and laboratory examination and imaging findings.

### Sample size

This study is powered to determine sensitivities of the respective imaging modalities with the 95% confidence level not extending the anticipated base sensitivity of 80% with more than 5%. We calculated that 246 patients with an urgent condition will be needed. Given the anticipated 25% urgent cases, at least 1,000 patients are needed in this study. This sample size will also provide sufficient data about rare conditions. Judging by the literature search on acute abdomen performed during preparatory activities prior to this study, we expect to include 110 patients (11%) with less frequent diagnoses. Sample size heuristics for multivariable modelling indicate that including 1,000 patients allows the inclusion of at least 15 variables covering both initial presentation and imaging results.

### Economic evaluation

For the economic evaluation we will obtain in-hospital direct medical costs. Direct and indirect non-medical costs will be collected by two patient questionnaires sent to the participants three and six months after hospital admission.

We will compare the diagnostic accuracy and the costs of several imaging strategies. We anticipate an imaging strategy with less imaging but the same accuracy as the reference strategy (all imaging in all).

## Discussion

### Rationale behind the study design

An alternative, possibly preferable study design is that of a randomised control trial (RCT). However, comparing all possible and daily used diagnostic strategies will need numerous trial arms with large amounts of patients and therefore is not practically feasible. Randomising patients to diagnostic strategies that are not evidence-based exceeds our study objectives. Our study is designed to collect evidence to provide guidelines for such diagnostic strategies. Therefore we chose this design which contains a full, probably over-complete, diagnostic protocol of 1,000 consecutive patients. Comparing imaging modalities separately as well as subsequently is possible because of stepwise and independently recording of the diagnosis, level of confidence of the diagnosis and a management plan after each diagnostic step.

The accurate detection of urgent conditions will lead to better therapeutic decision making. By making this a basic premise in our statistical analysis we believe that the optimal diagnostic strategy will lead to the health gains. However, our design prevents an empirical comparison of the health outcomes of different strategies. Because of our complete diagnostic protocol it does not allow us to document consequences in patient outcome in case of false positive or false negative radiological findings. A RCT would allow us to estimate these outcome consequences, but at the price of a major limitation in the number of comparable strategies.

The reference standard in a diagnostic study is generally a challenge, because patients with a positive index test tend to receive a different reference test (e.g. surgery) than patients with a negative index test (e.g. clinical follow-up). This verification bias can lead to overestimation of the diagnostic test accuracy. Therefore, we chose a uniform reference standard for all patients. By means of an expert panel, in which radiologists and surgeons experienced in acute abdominal conditions will assign the reference diagnosis post hoc.

Diagnostics, both clinical and radiological, will be performed by residents as well as specialists. This reflects daily practice in participating hospitals and will make our results more generalisable. The influence of experience of the investigator on accuracy results will additionally be studied in our analysis. Random selection of consecutive patients diminishes the risk of spectrum and selection bias. We believe that the definition of acute abdomen as used in this study renders the inclusion of cases across the whole clinical spectrum of patients with acute abdominal pain. Results obtained from our study population will therefore be applicable to the general population presenting with acute abdominal pain at the ED.

While a full consecutive series of patients is impractical, a random selection of consecutive patients is made in each participating centre. This selection depends on each hospitals case-load and capacity of imaging resources, but is independent of physician or patient preference. Limited capacity at the Department of Radiology forces some participating hospitals to include a maximum of 2 or 3 patients a day. Physician preference is minimized by daily including the first consecutive presenting eligible patients with acute abdominal pain. Selection bias may be caused by variation in policy to discharge patients presenting with acute abdominal pain from the ED without any further imaging. Such threshold can differ between hospitals. Observer bias will be minimized because of standardized evaluation of imaging independently of preceding test results.

Our study design will provide us the evidence base for constructing optimal diagnostic guidelines for patients with acute abdomen.

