#### Exclusion criteria

- Age < 18 years.

- Pregnancy.

- Abdominal pain due to blunt or penetrating trauma.

- Hemorrhagic shock caused by gastrointestinal bleeding or ruptured aortic aneurysm.

- Patients in whom no imaging was warranted by the treating physician ánd who were subsequently discharged home from the ED.

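### The claim that results apply to all ED patients with acute abdominal pain is not supported, because patients judged not to need imaging and sent home are excluded

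*Protocol article*

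**What the plan says.** All references are to the protocol article.

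- **Exclusion criteria, last item.** It removes "Patients in whom no imaging was warranted by the treating physician" and "who were subsequently discharged home from the ED". The two conditions are joined by an emphasised *and*, so both must hold.
- **Discussion, Rationale behind the study design.** The definition of acute abdomen used in the study is said to be one that "renders the inclusion of cases across the whole clinical spectrum of patients with acute abdominal pain". From this the article concludes: "Results obtained from our study population will therefore be applicable to the general population presenting with acute abdominal pain at the ED".
- **Same section, next paragraph.** A caveat follows: "Selection bias may be caused by variation in policy to discharge patients presenting with acute abdominal pain from the ED without any further imaging", and then "Such threshold can differ between hospitals". The applicability sentence is left as it stands.
- **Background.** The purpose is an algorithm for the wide range of ED patients with acute abdominal pain, so that the decision to image further can rest on features at presentation.
- **Data analysis.** Predictive values are planned for each imaging technique, alongside sensitivity, specificity and likelihood ratios.
- **Sample size.** "Given the anticipated 25% urgent cases, at least 1,000 patients are needed in this study".

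**The concern.** The applicability sentence is drawn from the pain definition (more than 2 hours, less than 5 days). That definition is broad, but eligibility also depends on the exclusion list. Its last item removes patients on the treating physician's judgement about imaging, combined with discharge. These are plausibly the patients in whom suspicion of an urgent condition was lowest, so the step from a broad definition to the general ED population does not follow.

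Two planned outputs are affected. Predictive values depend on the proportion urgent, which is probably higher among enrolled patients than among everyone who presents. The algorithm is meant to say who needs imaging, but it will be developed only in patients for whom imaging was judged warranted or who were not sent home. Its performance in patients now discharged without imaging will be unobserved. If the article's statement is carried into a guideline for ED physicians, readers will apply both outputs to a population in which they were not evaluated.

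**Working it through.** **1. The passages side by side.** The Discussion claims the whole spectrum and hence general applicability. The Exclusion criteria remove one part of that spectrum on clinical judgement. The caveat concerns thresholds that vary between hospitals. If every hospital used the same threshold, the caveat would have nothing left to describe, yet patients discharged without imaging would still be missing. It therefore does not cover the gap.

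**2. The plan's own figures.** For sensitivity p = 0.80 and half-width d = 0.05:

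n = 1.96² × p(1 − p) / d² = 1.96² × 0.16 / 0.0025 = 245.85, so 246 urgent cases.

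246 / 0.25 = 984, rounded up to 1,000.

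Both stated figures reproduce. The division also shows that the article applies the 25% to enrolled patients, and it is used that way below.

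**3. Inputs for the illustration.**
- Urgent proportion among enrolled patients: 25% (Sample size).
- Sensitivity: 80% (Sample size).
- Specificity: 90%, assumed; the article gives none.
- Share f of otherwise eligible ED patients removed by the criterion: 20-50%, assumed.
- Urgent proportion r among those removed: 1-5%, assumed.
- Sensitivity and specificity are taken to be the same in the removed patients, also assumed.

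**4. Formulas.**
- All-comers prevalence: π = 0.25(1 − f) + f·r
- PPV = 0.80π / [0.80π + 0.10(1 − π)]
- NPV = 0.90(1 − π) / [0.90(1 − π) + 0.20π]

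**5. Results.**

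| Population | π | PPV | NPV |
|---|---|---|---|
| Enrolled | 0.25 | 0.200/0.275 = 72.7% | 0.675/0.725 = 93.1% |
| All-comers, f = 20%, r = 5% | 0.20 + 0.01 = 0.21 | 0.168/0.247 = 68.0% | 0.711/0.753 = 94.4% |
| All-comers, f = 50%, r = 1% | 0.125 + 0.005 = 0.13 | 0.104/0.191 = 54.45% | 0.783/0.809 = 96.8% |

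The two all-comers rows are the extremes of the assumed range.

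**6. Dependence on the assumptions.** With f = 10-50% and r = 0-5%, all-comers prevalence is 12.5-23.0%.
- Specificity 80%: PPV falls from 57.1% to 36.4-54.4%, and NPV rises from 92.3% to 93.1-96.6%.
- Specificity 70%: PPV falls from 47.1% to 27.6-44.3%, and NPV rises from 91.3% to 92.1-96.1%.

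The direction is the same whenever r is below 25% and accuracy carries over. Only the size changes.

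**The case against.** The strongest reply is that the criterion is openly stated, that the Discussion itself names selection bias from discharge without imaging, and that low-risk patients are not absent. Because both conditions must hold, patients judged not to need imaging but kept in hospital remain eligible, as do patients sent home after imaging was warranted. The Data analysis section expects many patients with non-specific abdominal pain. Sensitivity, specificity and likelihood ratios are also reported, and a reader can apply them to another prevalence, subject to spectrum effects. All of this stands, and it limits the point to generalisability. It does not rescue the applicability sentence, which remains unqualified.

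Four stronger readings are tempting but unsupported:

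- *A second contradiction.* A reader might set the exclusion against the statement that selection "but is independent of physician or patient preference". In context that phrase describes the random selection of consecutive patients under limits of case-load and imaging capacity, including the daily maximum of 2 or 3 at some hospitals. It concerns sampling among eligible patients, not eligibility. It would be clearer if qualified, but it is not false.
- *An undefined 25%.* The sample-size division applies it to enrolled patients, so its meaning is clear enough.
- *An algorithm that would send unevaluated patients to imaging.* The algorithm does not yet exist. It is to be conditional on presentation, and the Economic evaluation section anticipates less imaging than imaging everyone. What it would do in the excluded group is unknown.
- *A demonstrated loss of PPV.* The excluded share, the urgent proportion among those excluded and the specificity are all assumptions. Lower risk among those excluded is itself an inference from the physician's decision.

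**Conclusion.** The point holds as a conflict between the exclusion criteria and the stated target population. The design supports conclusions about ED patients with acute abdominal pain who meet the eligibility criteria. It does not support the wider claim for predictive values or for an algorithm on who needs imaging.

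The size cannot be computed from the documents. Under the main illustration, enrolled-group PPV would overstate the all-comers value by about 5 to 18 percentage points (72.7 − 68.0 = 4.7; 72.7 − 54.45 = 18.25). NPV would be understated by about 1 to 4 points (94.4 − 93.1 = 1.3; 96.8 − 93.1 = 3.7). These figures rest on the assumed excluded share, urgent proportion and specificity, and on accuracy carrying over to patients who were never imaged in the study.

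Nothing here challenges accuracy estimates within the enrolled group, or the 246 and 1,000.

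**What to change.** 1. Replace the applicability sentence with one limited to ED patients with acute abdominal pain who meet the eligibility criteria, that is, in whom imaging was judged warranted or who were not discharged home. State the same target population for the algorithm and the predictive values.
2. Keep a prospective count, per hospital, of patients excluded under this criterion, and report it. It may be hard to recover afterwards.
3. Label PPV and NPV as applying to the enrolled group. If all-comers values are shown, give them only as a bounded sensitivity analysis: the observed count supplies f, r is varied over a stated range, and the assumption that sensitivity and specificity carry over is made explicit. Do not derive an all-comers imaging rate for the algorithm from this count, since that would need the clinical features of the excluded patients.
4. Qualify the phrase about independence from physician or patient preference with *among eligible patients*, rather than deleting it.

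The cost is a narrower stated target population and a simple screening count. Enrolment, imaging and sample size do not change.

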**Methods/design:**

Thousand consecutive patients with abdominal pain > 2 hours and < 5 days will be enrolled in this multicentre trial. After clinical history, physical and laboratory examination all patients will undergo a diagnostic imaging protocol, consisting of plain X-ray (upright chest and supine abdomen), US and CT. The reference standard will be a post hoc assignment of the final diagnosis by an expert panel. The focus of the analysis will be on the added value of the imaging modalities over history and clinical examination, relative to the incremental costs.

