### Study group

A random selection of consecutive adult patients who are presented, by themselves or a general practitioner, to the emergency department with non-traumatic abdominal pain persisting for at least 2 hours and less than 5 days.

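### The sample is labelled random and consecutive, but the only stated rule is first-come inclusion, capped daily in some hospitals, which does not protect against selection by arrival time

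*Protocol article*

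**What the plan says.** The protocol article describes the sample in three ways.

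- **Consecutive.** The Abstract (Methods/design) states: "Thousand consecutive patients with abdominal pain > 2 hours and < 5 days will be enrolled in this multicentre trial". The Discussion (Rationale behind the study design) also speaks of 1,000 consecutive patients.
- **Random.** The Study group section has "A random selection of consecutive adult patients". The Discussion repeats this and concedes that a complete series is not feasible: "While a full consecutive series of patients is impractical, a random selection of consecutive patients is made in each participating centre".
- **First-come with a cap.** The Discussion gives the working rule: "Limited capacity at the Department of Radiology forces some participating hospitals to include a maximum of 2 or 3 patients a day", and then "Physician preference is minimized by daily including the first consecutive presenting eligible patients with acute abdominal pain".

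The label carries weight in the same section: "Random selection of consecutive patients diminishes the risk of spectrum and selection bias". The section goes on to say that the results will apply to the general population presenting to the ED with acute abdominal pain. The one source of selection bias it names is variation between hospitals in discharging patients without imaging. Neither the daily cap nor the time of arrival is mentioned as such a source.

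**The concern.** Random selection means that chance decides who enters. Consecutive means that every eligible patient enters. Taking the first arrivals of the day until a cap is reached is neither: whether a patient enters follows from the order of arrival. The article describes no chance mechanism, yet it credits one with reducing bias.

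If patients who arrive early in the inclusion day differ from later ones, capped hospitals would contribute a shifted case mix. The quantities exposed are those that depend on case mix: the share of urgent conditions (anticipated at 25% under Sample size), the predictive values planned under Data analysis, and the claim that results carry over to all such patients. The study is meant to support a guideline for that whole population, so who enters matters to its purpose.

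**Working it through.** **1. The descriptions side by side.** A consecutive series of 1,000 and the statement that a full consecutive series is impractical cannot both hold. Random selection and inclusion of the first who present cannot both describe the same step. In a hospital without a cap, taking the first eligible patients with no limit would amount to a consecutive series. In a capped hospital it is a truncated one. The article does not say how many of the six hospitals are capped.

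**2. The plan's own figure.** Sample size: sensitivity 0.80, 95% confidence, half-width 0.05.

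n = 1.96² × 0.80 × 0.20 / 0.05² = 245.9, so 246 urgent cases; 246 / 0.25 = 984, stated as at least 1,000.

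This reproduces, and the sampling point does not change the arithmetic. The link is the 25%. If the true share in the sample were 15% to 35% (an assumed range), 1,000 patients would give 150 to 350 urgent cases and a half-width 1.96 × √(0.16/m) of 6.4 down to 4.2 points, against 5.0 at 250.

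**3. How far a cap could select on arrival.** The article gives no daily case-load, so the mean λ of eligible patients per hospital per day is an assumption, shown from 1 to 10. Arrivals are taken as Poisson at a constant rate over the inclusion day, with cap c = 2 or 3 (Discussion).

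- Share included = E[min(N, c)] / λ, with N Poisson(λ).
- Chance of inclusion for an arrival at fraction t of the day = P(Poisson(λt) < c).

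Example, λ = 4 and c = 2: P(0) = 0.0183 and P(1) = 0.0733. E[min(N, 2)] = 2 − 2 × 0.0183 − 0.0733 = 1.890, and 1.890 / 4 = 47%. At the end of the day the chance is 0.0183 + 0.0733 = 0.09.

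| λ (assumed) | Share included, cap 2 / cap 3 | Chance at mid-day, cap 2 / cap 3 | Chance at end of day, cap 2 / cap 3 |
|---|---|---|---|
| 1 | 90% / 98% | 0.91 / 0.99 | 0.74 / 0.92 |
| 2 | 73% / 89% | 0.74 / 0.92 | 0.41 / 0.68 |
| 4 | 47% / 66% | 0.41 / 0.68 | 0.09 / 0.24 |
| 6 | 33% / 49% | 0.20 / 0.42 | 0.02 / 0.06 |
| 8 | 25% / 37% | 0.09 / 0.24 | 0.003 / 0.014 |
| 10 | 20% / 30% | 0.04 / 0.12 | 0.0005 / 0.003 |

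At low volume the cap hardly matters. At higher volume it selects strongly on arrival order. These figures measure selection on arrival, not bias. Bias also needs case mix to differ by arrival time, on which the article has no data.

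**The case against.** The best defence is that the article is open about what is done. It says that a full series is impractical, that selection depends on case-load and imaging capacity, and what the rule and the cap are. First-come inclusion does take the choice away from physician and patient, which is the purpose given for it. The text claims only that the risk of bias is diminished, not removed. The cap applies to some hospitals, and a detail such as when the inclusion day starts may stand in the full protocol. All of this stands, and it limits the point. It does not rescue the word random: the article itself states the rule and then draws a conclusion that the rule cannot carry.

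Three stronger readings are tempting, and the documents support none of them.

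- **Later arrivals have no chance of inclusion, so weighting cannot repair the sample.** That is true only once a given day's cap is filled. On quieter days late arrivals enter. At an assumed mean of 4, an end-of-day arrival is included with probability 0.09 (cap 2) or 0.24 (cap 3), so weights exist (about 1/0.09 ≈ 11 for cap 2). Only near a mean of 10 do these chances become too small to use.
- **Protection against selection bias is absent.** The protection against preference is real. What lacks support is protection against selection by arrival time.
- **The comparison of modalities, or the planned analysis of reader experience, is invalid.** Every patient has X-ray, US and CT, so within-patient comparisons are not disturbed. Nothing in the article links arrival time to reader grade, and restriction to one part of the day could even reduce confounding by time of day.

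**Conclusion.** The point holds as a mismatch between label and rule. The sample is neither random nor fully consecutive as described, and the statement that random selection reduces spectrum and selection bias is not supported as far as time of arrival is concerned. The claim of applicability to the general ED population leans on that statement and is too broad as written.

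The size and direction of any bias are unknown. The illustrated shares of 90% down to 20% (cap 2) and 98% down to 30% (cap 3) rest on an assumed mean of 1 to 10 eligible patients a day, Poisson arrivals at a constant rate, and apply only to capped hospitals. At the low end the loss is small. The urgent share, the predictive values and generalisability may be affected. The sample size arithmetic is not in question.

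**What to change.** 1. In the Abstract, Study group and Discussion, replace random and consecutive by one description: *first eligible patients per day, up to a daily cap in some hospitals*.
2. Name time of arrival as a possible source of selection, beside the discharge policy already named.
3. Log the arrival time of every eligible patient, and report included against all eligible patients by arrival hour.
4. Where inclusion probabilities are large enough, add a sensitivity analysis weighted by arrival hour.
5. Qualify the generalisability sentence to match.

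The cost is a change of wording, one logged field for all eligible patients, one table and one sensitivity analysis. The daily number of patients is unchanged.

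An option, where radiology capacity allows, is a pre-generated random daily start time in capped hospitals, with the first 2 or 3 eligible patients after that time included. This would supply the chance element that the label claims. Its downside is some evening or night inclusions, when imaging capacity may be short, and possibly fewer patients on days with a late start. The relabelling and reporting above do not depend on it.
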